### **2.4 Endpoints**

#### **2.4.1 Primary Endpoint**

- i) Delivery < 37 completed weeks' gestation (powered).

#### **2.4.2 Secondary endpoints**

- i) Adverse perinatal outcome, defined as a composite outcome of death (antepartum/intrapartum stillbirths plus neonatal deaths prior to discharge from neonatal services) or one (or more) of intraventricular hemorrhage,

[figure not shown]

periventricular leukomalacia, hypoxic ischemic encephalopathy, necrotizing enterocolitis, bronchopulmonary dysplasia and sepsis.

- ii) Delivery <30 & 34 completed weeks' gestation.
- iii) Gestation at delivery.
- iv) Time between intervention and delivery.
- v) Requirement for Rescue Cerclage (bulging fetal membranes).
- vi) Other maternal and fetal outcomes: clinical course, therapies administered, maternal and fetal morbidity and mortality data until discharge or 28 days post-natal (whichever soonest).
- vii) Participant and clinician's perceptions of treatment: questionnaires with a selection of participants at 0-2 weeks post procedure. Questionnaires at one year are planned if funding is obtained.
- viii) Health costs at 28 days post-natal.
- ix) Biochemical end-points (on available samples): cervical swabs will be taken to determine the presence of cervicovaginal infection and concentrations of biomarkers of preterm birth, infection and inflammation. Saliva samples will be collected for salivary hormone levels, and blood samples taken for inflammatory markers and genetic analysis. Results will be correlated with maternal and fetal outcomes.

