### **2.2 Objectives**

The primary objectives of this study are:

- To determine if treatment with cervical cerclage, cervical pessary or vaginal progesterone in women at high risk of preterm birth who develop a short cervix by ultrasound measurement are equally efficacious to improve obstetric outcome by lengthening pregnancy and reducing the incidence of preterm delivery before 34 weeks' gestation.
- To evaluate the impact of the interventions on short term neonatal outcomes, assessed as a composite of perinatal death (within 28 days) and major morbidity

The secondary objectives are:

- To undertake an exploratory analysis to determine whether the response to intervention for a short cervix is related to the pre-intervention biomarker status (CVF, blood, saliva)
- To evaluate the acceptability to women and clinicians of each of the three treatment arms
- To assess the impact of both management strategies on health economic outcomes for mother and infant in terms of number of nights in each hospital setting; cost data to hospital discharge/28 days post natal (it is anticipated that a 6 month and 2 year follow up may be performed if funding is obtained).

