## 2.5 Participants

### 2.5.1 Eligibility criteria

Women with singleton pregnancies who are found to have cervical length <25 mm on transvaginal ultrasound between 14+0 weeks' gestation (dated by ultrasound or LMP and adjusted for ultrasound estimated date of delivery once ultrasound performed if no miscarriage prior to dating ultrasound) until 23+6 weeks' gestation with written consent to participate and one or more of the following risk factors;

History of:

- Previous preterm premature rupture of the fetal membranes ( $\leq 37$  weeks')
- History of previous PTB/second trimester loss ( $\geq 16$  weeks' or  $\leq 37$  weeks' gestation).
- Any cervical procedure to treat abnormal smears i.e. large loop excision, laser conisation, cold knife conisation or radical diathermy.
- Incidental finding of a short cervix on ultrasound scan (e.g. at the time of anomaly scan).

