### **3.3 Study visit 1: Randomisation and intervention (14+0-23+6 weeks' gestation)**

At time of recruitment women will be randomly assigned (1:1:1) to cerclage, progesterone or pessary. Randomisation will be carried out online via the Medscinet web portal ([www.medscinet.net](http://www.medscinet.net)). Users will be assigned a personal identifier number. Due

[figure not shown]

to the nature of the interventions, the study is not blinded to the clinician or patient. Recruiters and trial coordinators will not have access to the randomisation sequence. Women will be informed at time of recruitment to which arm they have been randomised. A 'minimisation' procedure, using a computer-based algorithm, will be used to avoid chance imbalances in important stratification variables. Stratification variables will be a) gestation, b) BMI <30 or >30 kg/m^2 c) risk factor (previous premature delivery <24 weeks & previous cervical surgery). Women will not know what treatment they will be allocated prior to recruitment. Medscinet will write the randomisation program and hold the allocation code. Contact information will be obtained from the patient. Demographic measures will be entered into the central trial database. Following randomisation, the obstetrician will then arrange for the intervention to be performed as the randomisation indicates. There is no 'emergency code break' procedure as the trial is an open label RCT.

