#### 3.4.1 Cervical cerclage

The cerclage procedure will be booked at the time of recruitment. It will be performed (according to local practice and procedures) within 7 days of recruitment to the trial. A vaginal cerclage will be inserted in the operating theatre by a clinician trained in the procedure, according to the technique preferred by the clinician. It is usually inserted under regional anaesthetic. Tocolysis, antibiotics and antenatal corticosteroids can be considered at the clinician's preference, but will be documented and considered in the analysis. The patient will usually go home the same day and will be followed up with two to four weekly transvaginal ultrasound scans (or more frequent if clinically indicated) according to local protocols. The suture is removed easily by exposing the cervix and cutting the knot, usually without the need for anaesthetic. This is done electively when a woman is 37 weeks' gestation, or if she presents in symptomatic preterm labour before labour becomes established, to avoid cervical trauma. The suture should also be removed if there is clinical evidence of chorioamnionitis. Cervical cerclage insertion is an established surgical procedure, which is associated with minimal risks. These include infection, miscarriage, bleeding, difficulty with suture removal and preterm prelabour rupture of membranes.

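### The death component of the adverse perinatal composite does not name fetal loss before viability, so on the natural reading unequal mid-trimester losses between arms would be masked or slightly reversed on that endpoint

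*Protocol*

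**What the plan says.** Section 2.4.2(i) gives the adverse perinatal outcome as "defined as a composite outcome of death (antepartum/intrapartum stillbirths plus neonatal deaths prior to discharge from neonatal services". The alternatives to death are intraventricular haemorrhage and "periventricular leukomalacia, hypoxic ischemic encephalopathy, necrotizing enterocolitis, bronchopulmonary dysplasia and sepsis". No gestation is stated at which a fetal death becomes a stillbirth, here or elsewhere in the protocol.

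Section 2.2 lists the same outcome under the primary objectives, "assessed as a composite of perinatal death (within 28 days) and major morbidity". The Professional Summary speaks only of a composite of death and major morbidity. None of the three places mentions loss before viability.

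The title of section 3.3 gives the entry window: "Randomisation and intervention (14+0-23+6 weeks' gestation". Of the risks of cerclage, section 3.4.1 says: "These include infection, miscarriage, bleeding, difficulty with suture removal and preterm prelabour rupture of membranes". Section 2.5.1 has the risk factor "History of previous PTB/second trimester loss".

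Fetal deaths are also collected under section 2.4.2(vi), among other outcomes: "maternal and fetal morbidity and mortality data until discharge or 28 days post-natal (whichever soonest". The primary endpoint in section 2.4.1 is "Delivery < 37 completed weeks' gestation (powered", with no lower limit. Section 5 specifies intention to treat and says that the neonatal composite is not powered for equivalence.

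**The concern.** A woman randomised at 15 weeks spends her first weeks on trial at gestations where a loss would ordinarily be called a miscarriage or a second trimester loss. If she loses the pregnancy at 20 weeks, there is no stillbirth on the usual sense of the word. There is no neonatal death unless the infant was born alive, and no infant in whom the listed morbidities could arise. One of the worst outcomes that the treatments aim to prevent would then be recorded as the absence of an adverse perinatal outcome.

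Such a loss also removes the pregnancy from any later chance of being an event. An arm with more of these losses therefore has fewer women left who can score on the composite. The protocol names miscarriage as a procedural risk in one arm, so a difference in losses cannot be ruled out in advance. Section 5 says that no difference in neonatal outcomes is expected. A composite that leaves out early losses could appear to confirm this when it is not so.

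**Working it through.** **1. The wording side by side.**

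| Outcome after randomisation at 15 weeks | Event on the composite? |
|---|---|
| Fetal death at 20 weeks, no live birth | Only if a site calls it a stillbirth; no limit is given |
| Live birth at 20 weeks, then death | Yes, as a neonatal death |
| Listed morbidity in a live-born infant | Yes |

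Only the first row is in doubt. It turns on a term that the protocol does not define.

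**2. Inputs.** The protocol states no figure for this composite, so there is none to reproduce. Its 90% power with 170 women per arm belongs to delivery before 37 weeks and does not change. The 170 is used below only to turn rates into counts. The other inputs are assumptions:
- L, the proportion of randomised women with an uncounted loss: 8% in arm B and 4% in arm A.
- m, the composite risk among continuing pregnancies: 10% in both arms, kept equal to isolate the effect of the definition.

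**3. Formulas, all randomised women in the denominator.**
- Losses counted: L + (1 − L)m
- Losses scored event-free: (1 − L)m

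| | Arm B (L = 8%) | Arm A (L = 4%) | B − A |
|---|---|---|---|
| Counted | 0.08 + 0.92 × 0.10 = 17.2% | 0.04 + 0.96 × 0.10 = 13.6% | +3.6 points |
| Event-free | 0.92 × 0.10 = 9.2% | 0.96 × 0.10 = 9.6% | −0.4 points |
| Counted, per 170 | 29.2 | 23.1 | |
| Event-free, per 170 | 15.6 | 16.3 | |

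The losses left out are 170 × 0.08 = 13.6 in arm B and 170 × 0.04 = 6.8 in arm A.

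**4. General form.** Let D be the difference in loss rates. Counting losses gives a difference of (1 − m)D. Scoring them event-free gives −mD. The two differ by exactly D, whatever m is. If D = 0 there is no bias between arms, but each arm's rate is understated by L.

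**5. Range.** Take m from 10% to 25% and loss pairs from 3% vs 6% to 2% vs 10%.
- Counted: from 0.75 × 3 = 2.25 to 0.90 × 8 = 7.2 points against the arm with more losses.
- Event-free: from 0.10 × 3 = 0.3 to 0.25 × 8 = 2.0 points in its favour.

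**6. Partial capture.** Suppose a share c of the early losses are live births followed by death, and so do count. The recorded difference becomes (c − m)D. With m = 10%, the reversal disappears at c = 10%: 0.10 × 0.08 + 0.092 = 10.0% and 0.10 × 0.04 + 0.096 = 10.0%. Above that share the direction is right, but the difference is still smaller than the true (1 − m)D for any c below 1.

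**The case against.** The strongest reply is that the protocol nowhere says that these losses are excluded. With no gestational limit on stillbirth, a site could count every fetal death after randomisation and still follow the text. Section 2.5.1 joins second trimester loss to preterm birth in one risk factor. The stratification in section 3.3 refers to a premature delivery before 24 weeks. Both suggest that the authors do not always keep the categories apart. The mention of miscarriage in section 3.4.1 is a list of risks, not an outcome definition. This stands to the extent that the exclusion is inferred, not stated. It does not remove the problem: an open-label, multi-centre trial would then depend on each site's reading of an undefined word.

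A second reply is that the losses show up elsewhere. Delivery before 37, 34 and 30 weeks has no lower limit, and section 2.4.2(vi) collects fetal mortality. This also stands, and it limits the harm. It does not replace the composite, because delivery before 37 weeks counts a loss at 20 weeks the same as a healthy birth at 36.

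A reader might infer that women with early losses leave the denominator, so that 17.2% and 13.6% would read as 10% and 10%. The documents do not support this. Section 5 specifies intention to treat, and nothing restricts the composite to live births or continuing pregnancies.

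**Conclusion.** The point holds as a defect in the definition of one secondary endpoint. On the natural reading, a pre-viable loss without live birth is scored event-free, and a difference in such losses between arms is masked or slightly reversed on the composite. In the example, a 3.6-point disadvantage becomes a 0.4-point advantage. The reversal itself is under one woman per 170 (16.3 − 15.6 = 0.7), so the masking is what matters. All loss and composite rates are assumptions, as are equal risk among continuing pregnancies and, in the main example, no live births among the losses. The protocol does not give the spread of gestation at randomisation either.

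Two stronger readings are tempting. One is that the composite will flatter cerclage. The protocol names miscarriage as a risk of that procedure but gives no loss rate for any arm, so the direction is unknown. The other is that the trial's main conclusion is at risk. It is not: the primary endpoint is unaffected on its wording, no sample size changes, and the composite is unpowered. Its place under the primary objectives in section 2.2 is the reason to correct it and not leave it to interpretation.

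**What to change.** In section 2.4.2(i), define the death component as any fetal loss after randomisation at any gestation (miscarriage or second trimester loss, and stillbirth) or neonatal death. State that it is analysed over all randomised women by allocated arm. Report the components separately, and show losses before and after viability, with the gestation used for that split written down. Bring the Professional Summary and section 2.2 into line, including the period over which neonatal deaths count, which sections 2.2 and 2.4.2(i) give differently.

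The cost is an amendment to wording. Section 2.4.2(vi) already covers fetal mortality, and section 6 already provides for tracking pregnancy outcomes, so no new data should be needed. The downside is small: the composite rate rises, and pre-viable loss is pooled with neonatal morbidity. Reporting the components lets a reader separate them.

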### 3.6 Subsequent study visits

All participants will be seen in a follow up appointment, normally between 2 and 4 weeks post-intervention. Subsequently, all follow up visits will be at the discretion of the attending clinician. Each visit will be documented on the online database. A transvaginal ultrasound cervical length measurement should be performed, and results recorded on the trial database, at each visit. At each visit, information will be obtained on compliance, adverse events or pregnancy complications.

The final study visit will take place between 34+0 and 38+0-weeks' gestation. Patients randomised to progesterone will be asked to return all unused medication and empty blister packs, in order to collect compliance information. Patients randomised to pessary will return at 37 weeks for removal. Patients randomised to cerclage will be seen between 34 and 37 weeks, and an appointment made for removal in the appropriate clinical area (usually hospital birth centre). If delivery has occurred prior to this time, then study staff will contact the participants, to arrange a follow up visit and collection of unused medication. Other than the baseline post intervention visit and final study visit, all other trial visits will be times to routine clinic attendances according to local clinical protocols and clinician practice. Interim study data will therefore only be collected if the patient attends the appropriate department for routine purposes.

Note review will take place 28 days after delivery to capture to collect maternal, fetal and health economic data up until 28 days postnatal. A contact/visit with the participant is not required.

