## **6 Collection of outcome data**

Women will be followed up until postnatal discharge. Neonates will be followed up to discharge or 28 days (whichever is sooner). Prompts on the database will alert the research midwife/assistant when each trial participant reaches her delivery date. Birth registers and in-patient records will also be used to track hospital admissions and pregnancy outcomes. Outcome data (medical and economic) will be collected by review of obstetric handheld/electronic notes. The primary and secondary outcome data will be collected after discharge from neonatal care.

Measurement of outcome (medical and economic): will be collected via electronic patient records, and/or hand-held patient notes. If information is not available, e.g. if the delivery occurred elsewhere, the patient, patient's GP or other hospital will be contacted. Gestational age will be calculated using ultrasound estimated date of delivery predicted at the 12-15 week scan, or last menstrual delivery if miscarriage occurs prior to dating scan.

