### Schedule of Visits

| Procedure                                                             | Screening & randomisation
14 +0 -23 +6 weeks gestation | Intervention (day 0)
14 +0 -23 +6 weeks gestation | Baseline visit (day)
1-4 weeks after procedure | Follow up visits (if clinically indicated) | Final visit
34 +0 -38 +6 weeks' gestation | Note review (no visit required)              |
|-----------------------------------------------------------------------|---------------------------------------------------------------------------------|----------------------------------------------------------------------------|---------------------------------------------------|--------------------------------------------|--------------------------------------------------------------------|----------------------------------------------|
| Visit window (± days)                                                 | -7 to 0 days                                                                    | Day 0                                                                      | 7-28 days                                         | Approximately 2-4 weekly                   | 3                                                                  | Discharge from Hospital or 28 days postnatal |
| Informed consent                                                      | C                                                                               |                                                                            |                                                   |                                            |                                                                    |                                              |
| Medical history and concomitant medications                           | C                                                                               |                                                                            | C                                                 | O                                          | C                                                                  |                                              |

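### The health-cost horizon is worded inconsistently across the protocol, and any stop at day 28 cuts off much of the neonatal stay of the earliest survivors, which can distort the cost comparison if early-birth rates differ between arms

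*Protocol*

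**What the plan says.** The protocol describes the period over which health costs accrue in several places.

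- Section 2.2 defines the aim as "health economic outcomes for mother and infant in terms of number of nights in each hospital setting", with "cost data to hospital discharge/28 days post natal". The slash is not explained. Follow-up at 6 months and 2 years is mentioned only as a possibility that depends on funding.
- Section 2.4.2(viii) lists the endpoint as "Health costs at 28 days post-natal".
- Section 3.6 has a note review that captures "health economic data up until 28 days postnatal".
- The Schedule of Visits heads the note-review column "Discharge from Hospital or 28 days postnatal", with no rule for choosing between the two.
- Section 6 says "Neonates will be followed up to discharge or 28 days (whichever is sooner") and follows women only to postnatal discharge. It then adds: "The primary and secondary outcome data will be collected after discharge from neonatal care".

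Three nearby statements bear on the reading. Section 2.4.2(vi) applies a sooner-of rule to other maternal and fetal outcomes. The end-of-trial definitions in Section 3.7 (Expected duration of the trial) and Section 17 are also sooner-of. In contrast, the composite in Section 2.4.2(i) counts neonatal deaths up to the infant's release from the neonatal service, with no 28-day limit.

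**The concern.** A site could follow one of these statements and extract a different total from a site following another, and both would be compliant. The readings do not differ in one direction only. A mother or term infant usually leaves hospital well before day 28, so stopping at discharge omits readmissions that a day-28 rule includes. A very preterm infant usually leaves well after day 28, so a day-28 stop omits nights that a to-discharge rule includes.

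The second omission falls on the quantity that Section 2.2 makes its resource measure, namely hospital nights for mother and infant. These interventions are meant to alter neonatal nights by preventing early birth, and the earliest births have the longest stays. The up-front cost of each treatment falls entirely inside the window, while the neonatal consequences do not. Section 1.3 presents avoidance of costly surgery as a benefit of showing equal efficacy, so the cost comparison may influence the choice of treatment.

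**Working it through.** The protocol gives no length of stay, unit cost, early-birth rate or expected cost difference, so there is no stated figure to reproduce. The check compares the readings, then sizes the truncation under stated assumptions.

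**Step 1: what each reading counts**

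| Reading | Readmission before day 28 | Infant born at 26 weeks, home at 36 weeks (70 nights) |
|---|---|---|
| Sooner of discharge and day 28 | left out | 28 nights |
| Fixed day 28 | counted | 28 nights |
| To discharge | left out | 70 nights |
| Later of discharge and day 28 | counted | 70 nights |

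**Step 2: share of nights lost to a 28-day cap**

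Assumption: survivors go home at 35 to 40 weeks postmenstrual age.

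Stay = 7 × (week of discharge − week of birth). Share lost = 1 − 28/stay, or zero if the stay is 28 nights or less.

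| Week of birth | Stay (nights) | Share beyond day 28 |
|---|---|---|
| 24 | 77-112 | 64-75% |
| 26 | 63-98 | 56-71% |
| 27 | 56-91 | 50-69% |
| 28 | 49-84 | 43-67% |
| 29 | 42-77 | 33-64% |
| 30 | 35-70 | 20-60% |
| 32 | 21-56 | 0-50% |

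At least half is lost across the whole assumed range only for births at or before 27 weeks. At 28 weeks this needs discharge at 36 weeks or later, at 29 weeks 37 or later, and at 30 weeks 38 or later.

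**Step 3: effect on the comparison between arms**

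Let arm A have early-birth risk rA and arm B rB, let L be the stay of an early survivor, and let U be the extra up-front cost of arm A in night-equivalents. All of these are assumed.

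Full difference (A − B) = U + (rA − rB) × L. Capped difference = U + (rA − rB) × 28.

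Taking L = 84:

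| rA v rB | U | Full | Capped at 28 |
|---|---|---|---|
| 10% v 10% | any | U | U |
| 10% v 15% | 0 | −4.2 | −1.4 |
| 10% v 15% | 2 | −2.2 | +0.6 |
| 10% v 15% | 5 | +0.8 | +3.6 |

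The cap moves the result by (rB − rA) × (L − 28) = 0.05 × 56 = 2.8 night-equivalents per woman, always against the arm with fewer early births. For L from 56 to 112 the shift is 0.05 × 28 = 1.4 to 0.05 × 84 = 4.2. With equal rates it is zero.

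**Step 4: early deaths**

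An infant who dies before day 28 loses no nights to the cap. If a fraction s stays beyond day 28, the shift becomes (rB − rA) × s × (L − 28). As an illustration, Section 1.1 cites 39% survival for births before 26 weeks. With s = 0.39 and all deaths before day 28, the shift falls to 0.39 × 2.8 = 1.1.

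**The case against.** **Two clean, contradictory horizons.** A reader might infer that Section 2.2 sets a longer horizon than Section 2.4.2(viii). The documents do not establish this. Sections 2.4.2(vi), 3.7, 6 and 17 all use a sooner-of rule, and read with them the slash in Section 2.2 is most naturally also capped at day 28. The gap is then only costs between an earlier discharge and day 28. The last sentence quoted from Section 6 may likewise say when data are extracted, not how long costs accrue. This stands: the defect is an ambiguity. It still needs resolving, because even the sooner-of reading disagrees with the fixed day 28 about readmissions.

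**The cap always understates the cost difference.** A reader might infer this too, but it does not follow. Section 5 expects about equal efficacy, and with equal early-birth rates the cap changes little. With unequal rates, net cost may be understated, reversed or overstated, depending on up-front cost. What survives is narrower: the difference in neonatal nights shrinks, and net cost shifts against the arm with fewer early births. Expected equality does not remove the point, since equality is the hypothesis under test. A 20-point margin on birth before 37 weeks would leave room for a 5-point difference in very early births.

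**Nights are not cost.** Section 2.2 separates nights by setting. If early nights cost more, the share of cost lost is smaller than the share of nights lost. This stands.

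**A disclosed choice on an unpowered secondary endpoint.** Twenty-eight days is openly stated, and costing methods may sit in an analysis plan. Both are fair. But an analysis plan cannot recover nights that the collection instructions told sites not to record.

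**Conclusion.** The point holds as an inconsistency in the cost horizon, with a conditional risk to the cost comparison. Five places word the horizon differently, and the readings give different totals for readmissions and for long neonatal stays.

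Under a 28-day cap, about 50-75% of nights are lost for survivors born at 24-27 weeks and 20-67% at 28-30 weeks. These figures rest on assumed discharge at 35-40 weeks, so a general statement that half or more is lost would go too far.

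A 5-point difference in early births (assumed) would shift net cost by 1.4 to 4.2 night-equivalents per woman for stays of 56 to 112 nights. That is enough to change the sign in some cases. Deaths before day 28 reduce the shift, and equal rates remove it. The primary endpoint is unaffected.

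**What to change.** State one horizon, in the same words, in Sections 2.2, 2.4.2(viii), 3.6, 6 and the Schedule of Visits, and remove the slash:

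- Mother: all hospital nights and costs to 28 days after delivery, including readmissions.
- Infant: all nights by setting, and costs, to first discharge from neonatal care or day 28, whichever is later.
- Keep the 28-day total as a secondary summary.

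Amend the sooner-of neonatal follow-up in Section 6, and the end-of-trial wording in Sections 3.7 (Expected duration of the trial) and 17, so that data after day 28 can be collected. The composite in Section 2.4.2(i) already needs infants tracked to neonatal discharge, so the same alignment serves both. If the sponsor prefers to keep a 28-day limit, the minimum is to reconcile the wording and state the truncation as a limitation.

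The cost is a protocol amendment, slightly more extraction from records already under review, and a wait for the longest stays. Under the assumed range, the last infant could need up to 112 − 28 = 84 days beyond day 28. No clinical care changes.
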